# Treatment outcomes of esophageal cancer in Eastern Africa: protocol of a multi-center, prospective, observational, open cohort study

**DOI:** 10.1186/s12885-021-09124-5

**Published:** 2022-01-19

**Keywords:** Esophageal squamous cell carcinoma, Esophageal cancer, Survival, Quality of life, Comparative effectiveness, Africa, Eastern Africa

## Abstract

**Background:**

Esophageal squamous cell carcinoma (ESCC) is a major cause of cancer morbidity and mortality in Eastern Africa. The majority of patients with ESCC in Eastern Africa present with advanced disease at the time of diagnosis. Several palliative interventions for ESCC are currently in use within the region, including chemotherapy, radiation therapy with and without chemotherapy, and esophageal stenting with self-expandable metallic stents; however, the comparative effectiveness of these interventions in a low resource setting has yet to be examined.

**Methods:**

This prospective, observational, multi-center, open cohort study aims to describe the therapeutic landscape of ESCC in Eastern Africa and investigate the outcomes of different treatment strategies within the region. The 4.5-year study will recruit at a total of six sites in Kenya, Malawi and Tanzania (Ocean Road Cancer Institute and Muhimbili National Hospital in Dar es Salaam, Tanzania; Kilimanjaro Christian Medical Center in Moshi, Tanzania; Tenwek Hospital in Bomet, Kenya; Moi Teaching and Referral Hospital in Eldoret, Kenya; and Kamuzu Central Hospital in Lilongwe, Malawi). Treatment outcomes that will be evaluated include overall survival, quality of life (QOL) and safety. All patients (≥18 years old) who present to participating sites with a histopathologically-confirmed or presumptive clinical diagnosis of ESCC based on endoscopy or barium swallow will be recruited to participate. Key clinical and treatment-related data including standardized QOL metrics will be collected at study enrollment, 1 month following treatment, 3 months following treatment, and thereafter at 3-month intervals until death. Vital status and QOL data will be collected through mobile phone outreach.

**Discussion:**

This study will be the first study to prospectively compare ESCC treatment strategies in Eastern Africa, and the first to investigate QOL benefits associated with different treatments in sub-Saharan Africa. Findings from this study will help define optimal management strategies for ESCC in Eastern Africa and other resource-limited settings and will serve as a benchmark for future research.

**Trial registration:**

This study was retrospectively registered with the ClinicalTrials.gov database on December 15, 2021, NCT05177393.

**Supplementary Information:**

The online version contains supplementary material available at 10.1186/s12885-021-09124-5.

## Background

Esophageal cancer (EC) is one of the leading causes of cancer morbidity and mortality worldwide. Most recent estimates from GLOBOCAN report that EC is the eight most common cancer globally with 604,000 annual incident cases and the sixth leading cause of cancer-related mortality with 544,000 deaths each year [1]. Nearly 80% of all EC cases occur in low- and middle-income countries (LMICs), where esophageal squamous cell carcinoma (ESCC) is the dominant histology [2]. Incidence rates for ESCC exhibit substantial geographic variation globally with several regions impacted by a disproportionately high burden of this disease. Eastern Africa has been identified as one of these geographic “hot spots,” along with north-eastern Iran, Central Asia, north-central China, and southern South America [2, 3]. In Eastern Africa, EC is the fifth leading cause of cancer mortality [1], with ESCC comprising 90% of cases [4].

Limited research has been published on the treatment of ESCC in sub-Saharan Africa [5]. In this setting, more than 90% of patients present with advanced or inoperable disease, and few are candidates for treatment with curative intent [6–8]. Palliative treatment strategies for advanced ESCC thus dominate the therapeutic landscape and include stenting for malignant obstruction with self-expandable metallic stents (SEMS), radiotherapy, chemo-radiotherapy, and brachytherapy. Use of each of these treatment modalities is supported by data that originates from high-income countries (HICs) [9]. The unique challenges of delivering care in resource-constrained settings, however, limit the generalizability of these findings to many African settings. In a previous systematic review of all studies on EC treatment in Africa [5], we identified only four prospective case series evaluating treatment of advanced ESCC in Eastern Africa, three of which reported outcomes of palliative stenting at two sites in Kenya and Malawi [10–12] and one that reported outcomes of palliative radiation in Ethiopa [13]. To date, no study has prospectively compared treatment modalities for advanced ESCC in Eastern Africa. Furthermore, little is known regarding the impact of different ESCC treatments on patients’ quality of life (QOL) in this setting. Of all the studies identified in our prior systematic review, only one examined QOL as an outcome metric [13].

With recent enhancement of cancer services in sub-Saharan Africa, the absence of context-specific data on treatment outcomes for ESCC is manifest. Expanded availability of chemotherapy, radiotherapy, and SEMS in Eastern Africa [14], has brought to light important questions regarding optimal management strategies for ESCC in this context. To address these questions, we developed a study protocol that aims to investigate the therapeutic landscape of ESCC in Eastern Africa and compare outcomes of different treatment approaches in use across the region. The Treatment Outcomes of Esophageal Cancer in Eastern Africa (TOEC-Eastern Africa) study is a prospective, observational, open cohort study of treatment strategies for ESCC that will recruit patients at six centers in Kenya, Malawi and Tanzania. This multi-center study has been established as a collaborative effort within the African Esophageal Cancer Consortium (AfrECC) [15].

## Methods

### Study objectives

The goals of the TOEC-Eastern Africa study are:To describe the treatment patterns for ESCC at referral hospitals in Eastern Africa.To investigate the outcomes of different ESCC treatments in Eastern Africa, specifically overall survival, QOL, and safety, with a particular focus on palliative interventions including chemotherapy, radiotherapy with or without chemotherapy, esophageal stenting with SEMS, and supportive care.To examine process measures related to the delivery of ESCC treatment at referral hospitals in Eastern Africa, including time from presentation to initiation of treatment, total time to deliver an intervention, and total number of days hospitalized during and after ESCC treatment.To assess utilization of healthcare resources by ESCC treatment approach, as measured by hospitalization events (total number of times hospitalized and cumulative days hospitalized) and need for subsequent intervention for recurrent or persistent dysphagia.

### Study design

This study is designed as a multi-center, prospective, observational, open cohort study. Initiation of recruitment has been staggered across sites, with the earliest commencing in February 2019 and additional sites beginning recruitment in 2021. Enrollment is scheduled to complete in December 2022, with follow-up to complete in June 2023. In total, approximately 2476 patients are expected to be enrolled in the study. Patients will be followed to collect key clinical and treatment-related data including overall survival and QOL metrics until death or loss to follow up. QOL metrics will be assessed at the time of study enrollment, prior to the initiation of treatment, and during post-treatment follow up (1 month after initiation of treatment, 3 months after initiation of treatment, and then every 3 months until death or loss to follow up). The accrual period is expected to range between 22 and 47 months across sites. Duration of follow up will differ by site due to the staggered initiation of recruitment, however, study participants will be followed for at least 6 months and up to a total of 53 months.

### Study settings

Participating sites are member institutions of AfrECC [15]. A total of six sites across Eastern Africa will participate, including: Ocean Road Cancer Institute (ORCI) and Muhimbili National Hospital (MNH) in Dar es Salaam, Tanzania; Kilimanjaro Christian Medical Center (KCMC) in Moshi, Tanzania; Tenwek Hospital in Bomet, Kenya; Moi Teaching and Referral Hospital (MTRH) in Eldoret, Kenya; and Kamuzu Central Hospital (KCH) in Lilongwe, Malawi (Fig. 1). Each site serves as a referral center for ESCC within the region. A summary of key characteristics and diagnostic and therapeutic services available at each study site is provided in Table 1.

**Fig. 1 Fig1:**
[figure not shown]
Map of African Esophageal Cancer Consortium (AfrECC) study sites. “Map of African Esophageal Cancer Consortium (AfrECC) sites” published by Van Loon et al. The African Esophageal Cancer Consortium: A Call to Action. J Glob Oncol. 2018 Sep;4:1-9. Licensed under Creative Commons Attribution 4.0. Participant sites modified from original. License: https://creativecommons.org/licenses/by/4.0/

**Table 1 Tab1:** Characteristics of study sites in Eastern Africa

Site	Tenwek Hospital	Ocean Road Cancer Institute (ORCI)	Muhimbili National Hospital (MNH)	Kamuzu Central Hospital (KCH)	Moi Teaching and Referral Hospital (MTRH)	Kilimanjaro Christian Medical Centre (KCMC)
**Location**	Bomet, Kenya	Dar es Salaam, Tanzania	Dar es Salaam, Tanzania	Lilongwe, Malawi	Eldoret, Kenya	Moshi, Kilimanjaro
**Setting**	Rural	Urban	Urban (two campuses, Upanga and Mloganzila)	Urban	Urban	Urban
**Type of Hospital**	Faith-based hospital	National cancer (specialized) referral hospital	National referral hospital	National referral hospital	National referral hospital	Zonal referral hospital
**Recruitment start date**	February 2019	May 2019	November 2019	June 2021	November 2021	November 2021
**Recruitment end date**^**a**^	December 2022	December 2022	December 2022	December 2022	December 2022	December 2022
**Estimated annual new diagnoses of EC**	250	150	167	300	325	90
**Forecasted annual recruitment**	220	130	150	160	275	80
**Forecasted enrollment (total)**	862	476	472	253	320	93
**Duration of enrollment**	47 months	44 months	38 months	19 months	14 months	14 months
**Diagnostic modalities available**						
Endoscopy	Yes	No	Yes	Yes	Yes	Yes
Pathology	Referred to outside facility	Yes	Yes	Yes	Yes	Yes
X-ray / ultrasound	Yes	Yes	Yes	Yes	Yes	Yes
CT scan	Yes	Yes	Yes	Yes	Yes	Yes
PET scan	No	No	No	No	No	No
EUS	No	No	No	No	No	Mo
**Treatment modalities available**						
Chemotherapy	Yes	Yes	Yes^a^	Yes	Yes	Yes
Radiation						
Brachytherapy (for EC)	No	No	No	No	No	No
EBRT	No	Yes	No	Planned 2022	Yes	Referred to ORCI
Esophageal stents	Yes	No	Yes	Yes	Yes	Yes
Esophagectomy	Yes	No	Yes	No	Yes	No
**Supportive care**						
Availability of TPN	Yes	Yes	Yes	Yes	Yes	Yes
Capacity for gastrostomy tubes	Yes	No	Yes	Yes	Yes	Yes
Intensive care unit	Yes	No	Yes	Yes	Yes	Yes
Palliative care team	Yes	Yes	No	Yes	Yes	Yes

Updated May 2021

*CT* Computed tomography, *EC* Esophageal cancer, *EBRT* External beam radiotherapy, *EUS* Endoscopic ultrasound, *PET* Positron emission tomography, *TPN* Total parental nutrition

^a^Chemotherapy is offered at MNH; most EC patients, however, are referred to ORCI for chemotherapy

In Tanzania, MNH is a public teaching hospital and national referral hospital affiliated with Muhimbili University of Health and Allied Sciences (MUHAS). MNH hosts 1500 beds, admitting 1000 to 1200 inpatients per week and providing care to more than 1000 outpatients per day. Following diagnosis, many of the cancer cases warranting chemotherapy and/or radiation therapy are referred to ORCI, the national cancer referral center in Tanzania, which hosts 273 beds. Muhimbili Academic Medical Center (MAMC) is a recently established public hospital affiliated with MNH. MAMC is located on the Mloganzila campus approximately 30 km from ORCI and MNH. Endoscopy services are available at both MNH and MAMC. KCMC is a public teaching hospital and zonal referral hospital located in Moshi, Tanzania. KCMC hosts 630 inpatient beds and sees an estimated 500-800 outpatients per day. It serves as the teaching hospital for the Kilimanjaro Christian Medical University College and hosts the Kilimanjaro Clinical Research Institute (KCRI), an affiliated research institution.

In Kenya, Tenwek Hospital is a faith-based hospital and tertiary care center located in the southwestern Rift Valley Province in Bomet County. Tenwek Hospital hosts 361 inpatient beds and sees approximately 140,000 annual outpatient visits. MTRH is a 990-bed tertiary referral and teaching hospital in Eldoret, Kenya. The hospital serves residents of the Western Kenya Region, parts of eastern Uganda and South Sudan with a catchment area that covers 22 counties and extends 150 km to the Kenya-Uganda border, and a population of about 24 million people. MTRH has 1200 inpatients at any one time and provides care to 1500 outpatients per day. It has several specialist outpatient clinics under Chandaria Cancer and Chronic Disease Centre (CCCDC). Following diagnosis, oncology patients are referred to Oncology clinic for chemotherapy, radiotherapy or palliative/supportive care. Endoscopy services are available at MTRH and other private hospitals in Eldoret town. MTRH serves as a teaching hospital for Moi University College of Health Sciences and other medical training institutes.

In Malawi, KCH is an 800-bed tertiary referral hospital in Lilongwe. It serves six districts of the central region of Malawi with a population of about 6 million people. The Malawi Ministry of Health plans to open the first Malawi National Cancer Center in Lilongwe in late 2021 on the KCH campus. This will be the first dedicated cancer center offering multidisciplinary, comprehensive cancer care in the country, including radiotherapy, and will serve all of Malawi’s ~ 18 million people. KCH has working relationships, both clinical and research, with the College of Medicine under the University of Malawi and the Malawi College of Health Sciences.

### Outcome assessment

#### Primary endpoint

The primary endpoint for this study will be overall survival (OS), as defined by time elapsed from date of diagnosis to death or last follow up.

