### Eligibility criteria

Patients aged ≥18 years with a diagnosis of EC will be eligible for study inclusion. Expanded inclusion criteria will be used as not all patients with suspected EC undergo diagnostic biopsies due to the costs associated with biopsy and pathological review. Diagnostic criteria for EC will include either histopathological confirmation or clinical diagnosis based on barium swallow (esophagram) and/or upper endoscopy without biopsy. This clinical criteria has been shown to have a > 90% pre-test probability for the diagnosis of ESCC in Eastern Africa [17]. Access to a mobile phone is not a requirement for study entry; however, should a study participant lack access, this will be noted on baseline enrollment forms. Patients who have previously received treatment for EC will be eligible for study participation; in these cases, details of prior EC treatment will be abstracted from medical records, if available.

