### Recruitment and consent of study participants

Patients who present to participating AfrECC sites with symptoms concerning for or a new diagnosis of EC will be identified by the research team. Since many patients with ESCC are ill and subject to clinical deterioration, we will employ rapid case ascertainment strategies to identify all cases of EC seen for further care. Study teams are embedded in clinical care settings. At designated times each week, research coordinators will use the following strategies to identify eligible patients with suspected diagnoses of ESCC: 1) contact physicians caring for inpatients on both medical and surgical wards and review current ward rosters; 2) review the schedule of endoscopy cases to be performed, including diagnostic and therapeutic procedures (if applicable); 3) review pathology reports (if applicable); 4) contact clinicians seeing patients in the outpatient setting; and 5) review chemotherapy and radiation schedules to identify patients with plans to undergo ESCC treatment (if applicable).

Once potential study participants are identified, they will be approached by a research assistant to assess eligibility and willingness to participate in this study. Study participants will be thoroughly informed about all aspects of the study, including study follow up plans and all regulatory requirements for informed consent. Written informed consent will be obtained prior to study enrollment. The informed consent documents will be available in both English and the local language(s) at each site. Study participants will receive a phone card as a small token of compensation for participation, valued at 5 USD in Kenya and Tanzania and 10 USD in Malawi, in accordance with the local institutional standards.

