### Statistical methods

All patients consenting to study participation with a histopathologically-confirmed or clinical diagnosis of EC will be included in the analyses. Descriptive statistics will be used to describe the proportion of ESCC patients receiving treatment with each modality at participating AfrECC sites. We will assess the associations between demographic/clinicopathologic characteristics and the treatment modalities employed (chemotherapy, radiotherapy, chemoradiation, esophageal stenting with SEMS, esophagectomy, supportive care alone). Categorical variables and continuous variables will be compared among the groups using Pearson’s Chi-squared test, and Analysis of Variance (ANOVA) (or Kruskal Wallis test when normality assumption is not held), respectively. Possible transformation (e.g., logarithm transformation) will be performed if the data is skewed.

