OS will be defined in two ways: 1) from the date of initial diagnosis to the date of death or last patient contact; and 2) from date of initiation of treatment to date of death or the date of last patient contact. Kaplan-Meier method will be used to summarize OS and log-rank test will be used to compare survival curves among treatments overall and stratified by the study center. Furthermore, Cox proportional hazards (cph) modeling will be used to account for demographic and clinicopathological factors by including them as covariates. Proportionality of hazards for key covariates will be tested by examining the correlation between time and scaled Schoenfeld residuals and log-log plots of survival. Important covariates that violate the proportionality assumption will be used to stratify the cph model. In many settings in Eastern Africa, long delays can occur between diagnosis and initiation of treatment. To mitigate immortal time bias that can emerge in time-to-event analyses of observational studies, two analytical approaches will be employed. First, in analyses using OS defined by date of diagnosis, the time from diagnosis to the initial treatment will be added as a covariate. Secondly, in analyses of associations between different treatments and OS, treatment status will be included in Cox regression modeling as a time-varying covariate (defined as treated versus untreated). This approach allows for patients to accrue follow up time while awaiting treatment, while also accounting for any events that occur during the ‘untreated’ waiting period [20]. Our primary analysis will examine pairwise comparisons of: stenting vs. radiotherapy with or without chemotherapy, stenting vs. chemotherapy, and radiotherapy with or without chemotherapy vs. chemotherapy. Among patients receiving radiation, outcomes may differ between patients receiving radiotherapy alone as compared to concurrent chemoradiation. Exploratory analyses will examine these subgroups separately.

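### Overall survival is counted from diagnosis but patients are observed only from consent, and the plan states no delayed entry, so Kaplan-Meier and log-rank results from diagnosis are left-truncated

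*Protocol article*

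**What the plan says.** Under Primary endpoint, OS is "as defined by time elapsed from date of diagnosis to death or last follow up". Statistical methods gives two definitions: "from the date of initial diagnosis to the date of death or last patient contact", and "from date of initiation of treatment to date of death or the date of last patient contact". On the analysis it says "Kaplan-Meier method will be used to summarize OS and log-rank test will be used to compare survival curves among treatments overall", also stratified by centre, followed by Cox models.

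On who enters, and when:

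- Eligibility criteria: "Patients who have previously received treatment for EC will be eligible for study participation".
- Study settings, in the text after Table 1, on patients diagnosed at Muhimbili National Hospital (MNH): "many of the cancer cases warranting chemotherapy and/or radiation therapy are referred to ORCI", the Ocean Road Cancer Institute.
- Recruitment and consent: staff also find patients from chemotherapy and radiation schedules. Written consent comes before enrolment.
- Statistical methods: "All patients consenting to study participation with a histopathologically-confirmed or clinical diagnosis of EC will be included in the analyses".

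Statistical methods names two measures against immortal time. The diagnosis-to-first-treatment interval becomes a covariate when OS runs from diagnosis, and treatment enters the Cox model as a time-varying treated/untreated status. No passage gives a risk-set entry time at consent or enrolment.

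**The concern.** A patient who dies between diagnosis and consent never appears in the data. Every enrolled patient has therefore survived that gap by construction. Counting the gap as time at risk adds person-time in which no death could have been seen.

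Two results are at stake. The descriptive medians, which the abstract offers as a benchmark for future research, would be too long. The pairwise treatment comparisons would also be biased if gaps differ by treatment. Table 1 makes a difference plausible: ORCI offers external beam radiotherapy but neither endoscopy nor stents, whereas every stenting site has endoscopy.

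**Working it through.** **Inputs from Sample size.** Stenting 1102 patients; radiotherapy with or without chemotherapy 464 + 212 = 676; median OS 36 and 27 weeks; alpha 0.0167 per comparison. The article gives no diagnosis-to-enrolment interval, so every gap below is an assumption.

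**1. The plan's own power.** Under exponential survival the true hazard ratio (radiotherapy/stent) is 36/27 = 1.333. Schoenfeld's formula is power = Φ(√(D·p₁·p₂)·|ln HR| − z). Here p₁ = 1102/1778 = 0.620, p₂ = 0.380, z = 2.394 (two-sided) and D = 1500 events (assumed). Then √(1500 × 0.620 × 0.380) ≈ 18.8, and 18.8 × 0.2877 − 2.394 ≈ 3.02, so power is about 0.999. Across the accrual patterns tried it is 0.993 to 0.999, against the stated 0.99. The stated power is right, but it assumes no truncation bias.

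**2. Medians.** With exponential survival and a fixed gap d, the curve stays at 1 until d, so naive median = true median + d. For d = 8 weeks, radiotherapy goes from 27 to 35 and stenting from 36 to 44.

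**3. Unadjusted contrast at the protocol's medians.** Simulated cohorts of 1102 and 676, exponential gaps, patients dead before entry removed:

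| Mean gap, stent / radiotherapy (weeks) | Naive HR | HR, delayed entry | Naive medians, stent / radiotherapy | Power at naive HR, 1500 events |
|---|---|---|---|---|
| 4 / 4 | 1.34 | 1.34 | 39.4 / 30.7 | 0.999 |
| 2 / 4 | 1.29 | 1.34 | 37.9 / 30.8 | 0.99 |
| 2 / 8 | 1.17 | 1.32 | 37.8 / 34.3 | 0.73 |
| 2 / 12 | 1.11 | 1.33 | 38.1 / 36.9 | 0.34 |

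Equal gaps inflate the medians but barely move the hazard ratio. Delayed entry brings the medians back to about 36 and 27.

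**4. Unadjusted contrast under the null.** Both true medians are 30 weeks and the stent gap averages 2 weeks. If all radiotherapy patients enter a mean 8 weeks after diagnosis, the HR is 0.87. If half enter a mean 13 weeks after, it is 0.90.

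**5. The planned Cox measures.** In the same null settings, with treatment starting a mean 2 weeks after enrolment (assumed), the diagnosis-to-treatment covariate gives HR 0.99 to 1.00 with 0 to 2% rejection. OS from treatment start gives HR 1.00 with 2% rejection. When treatment follows enrolment, the wait for treatment contains the entry gap, which is why the covariate works.

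It works less well for patients treated before entry. Their interval to first treatment is short while their entry gap is long (mean 26 weeks assumed). The true HR is 1.33:

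| Mean gap for other patients, stent / radiotherapy (weeks) | Treated before entry, stent / radiotherapy | HR with covariate | HR, delayed entry |
|---|---|---|---|
| 2 / 8 | 0 / 0 | 1.30 | 1.32 |
| 2 / 8 | 10% / 10% | 1.28 | 1.34 |
| 2 / 8 | 5% / 20% | 1.20 | 1.32 |
| 2 / 4 | 5% / 30% | 1.21 | 1.33 |

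**6. Time-varying model.** It was coded with one indicator per modality and no change in hazard at treatment; gaps were 2 / 8 weeks. Radiotherapy versus stent stays at 1.30. Radiotherapy versus untreated is 2.32 without delayed entry and 1.17 with it, because guaranteed survival before enrolment is counted as untreated time.

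**7. Limit of entry at consent.** When only patients who reach treatment are compared, entry at consent leaves a null HR of 0.96 to 0.98. Survival from consent to treatment is still guaranteed.

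**The case against.** The strongest reply is that the plan already contains measures that work. A reader might infer from step 4 that the planned Cox analysis has a gravely inflated error rate, since the unadjusted null comparisons reject in 30% to 61% of simulated cohorts at alpha 0.0167. The article does not support that: those rates belong to a comparison without the planned covariate, and step 5 shows that covariate and OS from treatment start holding the error near or below nominal when treatment follows enrolment. This part of the reply stands.

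The referral argument is also weaker than it looks. MNH and Kilimanjaro Christian Medical Centre recruit for the study themselves, partly from endoscopy lists and pathology reports, so a patient sent on to ORCI may have enrolled near diagnosis. Rapid case ascertainment and the planned pre-treatment interview point the same way. Gaps remain for patients missed there, seen before those sites opened (November 2019 and November 2021), or diagnosed outside the network.

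The direction is assumed too. Previously treated patients might later be stented for recurrent dysphagia, which would lengthen the stent group's gap instead.

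Finally, risk-set coding could sit in an analysis plan not shown. But the article sets out both time origins, the tests and two bias remedies in detail. What it sets out does not cover the gap before enrolment in Kaplan-Meier or log-rank.

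**Conclusion.** The point holds in a limited form. As written, Kaplan-Meier and log-rank from diagnosis are left-truncated. Medians are overstated by roughly the entry gap, and comparisons favour later-enrolling groups if gaps differ by treatment. The planned Cox treatment contrasts are largely protected when treatment follows enrolment. They remain exposed for patients treated before enrolment, and any contrast with untreated person-time is distorted.

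The size cannot be fixed from the document: neither the diagnosis-to-enrolment interval nor the share of previously treated patients is given. The null HR of 0.87 to 0.90 and the fall from 1.33 to 1.17 are illustrations for unadjusted comparisons with the longer gap assigned to radiotherapy. It would also go too far to conclude that previously treated patients must be excluded. The eligibility and analysis-set statements include them, and delayed entry handles the truncation without removing them.

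**What to change.** - Keep diagnosis as time zero, but enter each patient into the risk set at the consent date in Kaplan-Meier, log-rank and Cox analyses.
- Keep treatment time-varying in the Cox model. Where treated groups are compared directly, enter patients at the later of consent and treatment start.
- For OS from treatment start, apply delayed entry at consent to anyone enrolled after treatment began.
- Report the diagnosis-to-enrolment interval by treatment and by site.
- Make exclusion of previously treated patients a sensitivity analysis. Prior-treatment details are abstracted only where records exist, so that subgroup may be imperfectly identified.

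The cost is small. Table 3 already collects the diagnosis date, written consent precedes enrolment, and Stata and R both support delayed entry. The price is slightly smaller early risk sets and somewhat wider intervals.
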